### Plans for collection, laboratory evaluation and storage of biological specimens for genetic or molecular analysis in this trial/future use {33}

A 2-ml sample of blood will be drawn on enrollment for a blood smear for malaria parasitaemia using standard microscopy, complete blood count and for a dry spot on filter paper. This will be repeated during the scheduled and unscheduled visits at which time if clinically indicated, additional samples will be drawn for culture (blood and urine) from participants with axillary temperatures > 38 °C. The filter paper samples will be used to classify parasitaemia as recrudescence or re-infections by comparing alleles of parasite genes encoding merozoite surface proteins 1 and 2 (*msp1*, *msp2*) and glutamate-rich protein (*glurp*) [28] using standard PCR methods and determining resistance to SP and piperaquine [29]. The antimicrobial susceptibility and resistance patterns of bacterial isolates in febrile children will be examined to determine the impact of malaria prophylaxis on antimicrobial drug resistance. The remaining cell pellet, plasma and serum samples will be stored and in future, used for immunological (e.g. antibodies against viral infections) and the role of sickle cell variants (genetic).

## Statistical methods

### Statistical methods for primary and secondary outcomes {20a}

#### Analysis populations

Primary analyses will be based on intention-to-treat (ITT) population, and secondary supportive analyses will be done on the per-protocol (PP) population, which is important for cost-effectiveness considerations. Incidence rates will be calculated and rate ratios estimated using Poisson regression, with treatment (as randomised) as the only predictor variable and the stratification factors of site and weight band as co-variates.Intention-to-treat (ITT) population: This population consists of all randomised subjects who have a valid outcomePer-protocol (PP) population: This population is a subset of the ITT population. Subjects with major protocol deviations will be excluded from the PP population. Major protocol deviations will be defined in the SAP

#### Assessment of efficacy

We will compare incidence rates between intervention groups using incidence rate ratios. Incidence rates will be calculated as the number of events divided by the total follow-up time in each arm. Rate ratios shall be estimated using Poisson regression, with treatment (as randomised) as the only predictor variable and the stratification factors of site and weight band as covariates. In the presence of overdispersion, negative-binomial regression will be used to estimate the incidence rate ratios. Patients who die, withdraw or get lost in follow-up will be censored at their date of death, withdrawal or the last follow-up visit. A *P*-value < 0.05 will be considered statistically significant.

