### Eligibility criteria {10}

#### Inclusion criteria

The inclusion criteria for enrolment are:Children with a diagnosis of SCA *(HbSS)* on haemoglobin electrophoresis, high-performance liquid chromatography (HPLC) or isoelectric focusingAged between 6 months and 15 yearsWeight of 5 kg or higherWritten informed consent from a parent or legal guardian and assent by the child (if aged 8 years or older)

The upper age limit of 15 years was chosen based on both a pragmatic approach of being able to recruit most patients attending SCA clinics and the lower incidence of malaria in adolescents beyond this age. Around Jinja, the incidence of malaria in children with normal haemoglobin (HbAA) declines by over 50% in adolescents 15–18 years compared to those 11–15 years ([name], unpublished).

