#### Exclusion criteria

Participants presenting with an acute illness on enrolment will first receive treatment for the acute event and be recruited when symptoms resolve.

The exclusion criteria were:Those with an additional chronic disease such as known congenital heart diseaseThose with a known allergy to DP or SPOther known red cell disorders, e.g. thalassaemia, G6PD deficiencyThose receiving daily cotrimoxazole prophylaxisThose unlikely to comply with the follow-up scheduleThose participating in another trial

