### Methods for additional analyses (e.g. subgroup analyses) {20b}

#### Subgroup analyses

For sub-analysis, we will use stratified analysis to assess to what extent the effect of the intervention on the primary outcome is influenced by site, demographic (e.g. age, and socio-economic status) or clinical parameters, malaria transmission variables (malaria transmission intensity, residence (urban/rural), season, insecticide-treated nets use, site), time of assessment and potential intervention modifiers.

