#### Sensitivity analyses

Several sensitivity analyses will be conducted to assess the robustness of the primary endpoint analysis. These include an analysis of the PP subject population and a covariate-adjusted analysis. Other regression models will also be explored. Additional post hoc analyses may also be conducted if deemed appropriate. In addition, we will compare the results of the covariate-adjusted analyses with and without imputation for missing values for covariate values at baseline.

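### The primary model is valid but omits the enrolment blood smear, a planned baseline measurement that could add modest precision if malaria counts are overdispersed

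*Protocol article*

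**What the plan says.** Under Assessment of efficacy (and in the same terms under Analysis populations), rate ratios come from Poisson regression "with treatment (as randomised) as the only predictor variable and the stratification factors of site and weight band as covariates". The same section provides for extra-Poisson variation: "In the presence of overdispersion, negative-binomial regression will be used to estimate the incidence rate ratios". Because the covariate list is stated explicitly, the primary model is a decision made in this document and not a detail left to an analysis plan.

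The section on biological specimens {33} states: "A 2-ml sample of blood will be drawn on enrollment for a blood smear for malaria parasitaemia using standard microscopy, complete blood count". It does not restrict this to a subset of children. Age is known for every child from the eligibility criteria. It appears in the analysis as a subgroup factor, where the effect may be "influenced by site, demographic (e.g. age, and socio-economic status) or clinical parameters".

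Wider adjustment is planned only as a check on robustness, under Sensitivity analyses: "These include an analysis of the PP subject population and a covariate-adjusted analysis". The covariates of that analysis are not named.

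**The concern.** The primary outcome is a count of malaria episodes. Parasitaemia at enrolment is a direct, pre-randomisation measure of a child's exposure and may predict later episodes beyond what site and weight band capture. Adjustment confined to a sensitivity analysis cannot sharpen the primary test.

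Predictable variation between children that stays out of the model adds to the dispersion that the negative-binomial model must carry, and so widens its interval. With a log link and no interaction, the rate ratio keeps its meaning when baseline covariates are added, so adjustment would not change the question. At stake is a small amount of precision, not bias and not the validity of the test.

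**Working it through.** **1. The plan's own sample size.** Inputs from Sample size {14}: rates 0.2 and 0.1 per person-year, power 0.9, significance level 0.05 (taken as two-sided), 18 months, 20% loss.

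n per arm = (1.960 + 1.282)² × (1/0.2 + 1/0.1) / ((ln 0.5)² × 1.5) = 10.507 × 15 / (0.4805 × 1.5) = 218.7, so 219 per arm and 438 in total. Then 438/0.8 = 547.5, rounded up to 548. Both stated figures reproduce. The formula is pure Poisson: it relies on no covariates and makes no allowance for overdispersion.

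**2. Variance with dispersion.** Over 1.5 years the means per child are 0.30 (SP) and 0.15 (DP). With dispersion k not explained by covariates,

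Var(log rate ratio) = (1/0.30 + 1/0.15 + 2k)/n = (10 + 2k)/219.

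Power = Φ(ln 2 / SE − 1.960).

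- k = 0: SE 0.2137, power 90.0%. There is no dispersion for a covariate to explain, so the gain is nil.
- k = 0.5: power 87.1%.
- k = 1: power 84.2%.
- k = 2: power 78.3%.

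**3. What the smear could explain.** Assumptions, because the document gives no figures: positivity p of 5, 10 or 20%; rate ratio r of 2 or 3 for later malaria in smear-positive children; residual dispersion k_res of 0.5 or 1.0 after adjustment.

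Dispersion due to smear: k_X = p(1−p)(r−1)² / (1 + p(r−1))². Unadjusted dispersion: (1 + k_res)(1 + k_X) − 1.

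- Least favourable corner (p = 0.05, r = 2, k_res = 0.5): k_X = 0.0475/1.1025 = 0.043; unadjusted k = 0.565. Variance units are 11.13 unadjusted and 11.00 adjusted, ratio 1.012, a fall of 1.2%. Power goes from 86.8% to 87.1% (+0.4 points before rounding).
- Most favourable corner (p = 0.20, r = 3, k_res = 1.0): k_X = 0.64/1.96 = 0.327; unadjusted k = 1.653. Variance units are 13.31 and 12.00, ratio 1.109, a fall of 9.8%. Power goes from 80.3% to 84.2% (+3.9 points).
- The other ten combinations lie between; all gain 3.0 points or less.

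On the 548 children planned, these falls are worth about 6 children (548 × 0.0116) to 54 children (548 × 0.0982). In the 12-month option, variance units are 15 + 2k, so the falls are smaller: 1 − 16/16.13 = 0.8% and 1 − 17/18.31 = 7.1%.

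**4. Second parameterisation.** If added covariates explain 10 to 30% of the dispersion left after site and weight band, variance falls by 0.9 to 2.7% (k = 0.5), 1.7 to 5.0% (k = 1) and 2.9 to 8.6% (k = 2). This is about 0.3 to 3.5 points of power.

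**5. Simulation.** There were 600 trials per scenario, with 219 per arm, four sites, weight quartiles correlated 0.9 with age, and 20% smear-positive (all assumed). Adding smear and age lowered the robust variance by 0% when neither had an effect, about 2% with smear rate ratio 2, about 7% with rate ratio 3, and about 11% with rate ratio 4 and a strong age effect. Ordinary model-based Poisson standard errors rose slightly (for example 0.2171 to 0.2181). The gain therefore appears only where the standard error reflects overdispersion. The mean log rate ratio barely moved.

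**The case against.** The strongest reply is that nothing here is wrong. The model adjusts for exactly the randomisation strata, the sample size never relied on further covariates, and an adjusted analysis is already planned. That stands: this is a suggestion about efficiency.

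The size also rests wholly on assumed inputs. The exclusion criteria section says: "Participants presenting with an acute illness on enrolment will first receive treatment for the acute event and be recruited when symptoms resolve". This is a reason to doubt the high end of the positivity range and to expect gains nearer the low end. That also stands.

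A reader might go further than the document allows in two ways.

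- **Age.** One might infer that the protocol itself documents a strong age gradient, since it says that "the incidence of malaria in children with normal haemoglobin (HbAA) declines by over 50% in adolescents". That statement compares ages 15–18 with 11–15 near one site, from unpublished data, in children without sickle cell anaemia. The older group lies essentially outside the trial's range of 6 months to 15 years. The document shows no gradient in the enrolled population, and weight band probably carries much of the age information already.
- **The model switch.** One might infer that the omitted covariates are what would force the move to negative-binomial regression. In the scenarios above, smear accounts for dispersion of 0.04 to 0.33, while 0.5 to 1.0 remains after adjustment. The switch would still be needed.

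These points shrink the concern. They do not remove it: a planned baseline measurement is left out of a model in which, under the overdispersion the plan itself provides for, it may help.

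**Conclusion.** The point holds as a low-priority efficiency recommendation. The stated model is valid, and its omission of enrolment parasitaemia may forgo a little precision. The likely size is a 1 to 10% fall in the variance of the log rate ratio, or 0 to 3 points of power in all but the most favourable scenario, where it approaches 4. This depends on overdispersion being present and on the assumed positivity, prognostic strength and residual dispersion. Under the pure Poisson assumption behind the sample size, the gain is zero. The case for smear is stronger than the case for age, which is optional.

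**What to change.** Before unblinding, state under Analysis populations and Assessment of efficacy that the primary Poisson or negative-binomial model includes enrolment smear result (positive or negative) as a fixed covariate beside site and weight band, with continuous age as an optional addition. Keep the model with site and weight band alone as the sensitivity analysis.

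Add a rule so that no randomised child is dropped for a missing smear, for example a separate missing category or single imputation. The missing-data section {20c} says only that covariates may be imputed, which is too loose for a covariate in the primary model.

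No new data are needed. The cost is a short change to the protocol and analysis plan, which under the amendment section {25} goes to the sponsor's and countries' ethics committees and the funder, plus the handling of any missing smears.

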### Sample size {14}

The minimum incidence rate of clinical malaria in SCA patients receiving monthly SP is estimated at 0.2 events per year. Assuming an effect size of 50% if DP is used (i.e. a 50% reduction in the rate as in Bigira et al. [27] that is, a hypothesised incidence rate of 0.1 events per person per year in the DP group), at a power of 0.9 and 0.05 level of significance, we will need 438 individuals to be followed up for 18 months. Allowing for 20% losses to follow-up, we shall need 548 participants (274 in each group) to be followed for an average of 18 months, equivalent to 9864 person months, or 824 participants for an average follow-up of 12 months, equivalent to 9888 person-months.

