#### Secondary efficacy outcomes

Intention-to-treat analysis shall be followed for analysis of secondary outcomes. For count secondary outcomes, all sick visits, malaria-specific sick visits, all-cause hospitalisations, malaria-specific hospitalisations, serious cardiac adverse events and SCA-related vaso-occlusive events, we shall fit Poisson regression models and compare events between the intervention groups using incidence rate ratios. Negative-binomial regression models will be fitted if there is overdispersion. Model adjusters shall be informed by imbalances in baseline characteristics between the intervention groups. We shall fit a binary logistic model to compare the odds of death between the two intervention groups. Death shall likely be a rare outcome in this study, and often, binary logistic regression models face convergence problems due to the sparse outcome. We shall instead fit models using the firth method, which avoids the convergence challenges of the logistic regression model when the outcome is rare. We shall report odds ratios as measures of association. We shall also test if the change in QTc length from baseline is > 60 ms using a one-sided *t*-test. We will provide a list of individual participant changes in QTc length from baseline. Exploratory quantitative outcomes shall be summarised by the intervention arm using descriptive statistics. Qualitative exploratory outcomes such as user and provider experiences of the intervention, satisfaction with the intervention and treatment preference will be described as text. We shall also present a list of adverse events and document if they were related to the study drug or not.

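### A Poisson default that yields to negative binomial only if the data show overdispersion can inflate the type I error under some common switch rules

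*Protocol article*

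**What the plan says.** Under Assessment of efficacy the default is stated as "Rate ratios shall be estimated using Poisson regression, with treatment (as randomised) as the only predictor variable", with site and weight band added as covariates. The next sentence makes the model conditional: "In the presence of overdispersion, negative-binomial regression will be used to estimate the incidence rate ratios". Significance is then judged at the conventional level ("value < 0.05 will be considered statistically significant"). The section on analysis populations names Poisson alone. Under Secondary efficacy outcomes the same conditional switch applies to the count outcomes: "Negative-binomial regression models will be fitted if there is overdispersion". No robust or scaled variance is mentioned in any of these places.

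The rate is events over total follow-up time, and censoring is at death, withdrawal or last visit rather than at the first malaria episode, so one child can contribute several episodes. The section on subgroup analyses lists season, net use, residence, age, socio-economic status and transmission intensity as factors that may matter for the primary outcome. The primary model has terms for site and weight band only.

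**The concern.** Repeat malaria episodes cluster within children, and the article itself names several sources of between-child variation that the primary model does not adjust for. Some residual overdispersion is therefore foreseeable before any data are seen. Even so, the plan starts from a model that assumes none and leaves it only if the data give a signal.

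The difficulty is the low event rate. With a fraction of an event per child, overdispersion large enough to distort a Poisson standard error produces only a modest variance/mean ratio. A diagnostic with a loose cut-off can pass it as acceptable, and the primary p-value and confidence interval then rest on a standard error that is too small. The same holds for the count secondary outcomes and for the interim look if it uses the same approach.

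**Working it through.** **1. The plan's own figure.** Inputs from Sample size: the SP rate ("The minimum incidence rate of clinical malaria in SCA patients receiving monthly SP is estimated at 0.2 events per year"), a DP rate half as large (0.1), 90% power, a 5% level, and a stated total of 438 before losses. For a Poisson log rate ratio, person-years per arm = (1.960 + 1.282)² × (1/0.2 + 1/0.1) / (ln 2)² = 328.05. Dividing by 1.5 years gives 219 per arm, 438 in total, and 438/0.8 = 548. The stated numbers are reproduced by a pure Poisson formula with two-sided 5%, so the design allows for no overdispersion.

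**2. Size of the signal.** Let the count variance be μ + aμ², where a is the residual dispersion (assumed). The variance/mean ratio is 1 + aμ. At 0.2 per year, μ = 0.2 over 12 months and 0.3 over 18 months.
- a = 1: 1.2 to 1.3
- a = 2: 1.4 to 1.6
- a = 3: 1.6 to 1.9

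At μ = 0.3 the ratio reaches 2 only at a = 1/0.3 = 3.3.

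**3. Plain Poisson with model-based errors, analytic.** Type I error = 2[1 − Φ(1.96/√(1 + aμ))]. For a = 0.5, 1, 2, 3:
- 18 months: 6.8%, 8.6%, 12.1%, 15.5%
- 12 months: 6.2%, 7.4%, 9.8%, 12.1%

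**4. Switch rules, simulated.** 2,000 null trials per setting, rate 0.2 per year, treatment-only model, 20% of children with shortened follow-up, Monte Carlo SE about 0.5 to 0.9 points. Type I error, with the share of trials keeping Poisson in brackets:

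| 18 months, 274 per arm | a = 1 | a = 2 | a = 3 |
|---|---|---|---|
| Plain Poisson | 9.1% | 12.0% | 15.6% |
| Switch if Pearson/df > 2 | 9.1% (100%) | 11.9% (99%) | 13.6% (83%) |
| Switch if deviance/df > 1 | 8.9% (99%) | 10.6% (81%) | 9.5% (51%) |
| Switch if Pearson/df > 1.5 | 8.9% | 8.3% | 5.2% |
| Switch if Pearson/df > 1.25 | 7.0% | 5.8% | 4.8% |
| Likelihood-ratio test of a = 0 | 5.8% (6%) | 5.7% (0%) | 4.8% (0%) |

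At 12 months with 412 per arm, Pearson/df > 2 gives 7.2%, 8.5% and 11.2%, and deviance/df > 1 gives 7.2%, 8.5% and 11.3%. Each rule keeps Poisson in about 99% of trials or more.

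At the benign end, plain Poisson gives 4.8% at a = 0 (18 months). At a = 0.5 it gives 7.0% (18 months) and 5.6% (12 months). Negative binomial throughout gives 4.4% to 5.7% at every dispersion tried, from 0 to 5.

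**5. With site and weight band in the model.** Two further simulations used 274 per arm over 18 months. One assumed site rates of 0.1, 0.1, 0.3 and 0.3 per year and three weight bands.
- Plain Poisson: 8.3% and 10.0% at a = 1, 12.4% and 12.8% at a = 2, 16.6% and 18.1% at a = 3.
- In one of them, the Pearson/df > 2 switch gave 8.3%, 12.5% and 14.4%, a likelihood-ratio trigger 4.5% to 4.9%, and negative binomial or robust variance throughout 4.5% to 5.1%.
- In the other, robust variance gave 4.6% to 6.0% for a = 1 to 3.

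**6. Interim.** The stopping threshold is 0.001. If Poisson is used at half the exposure, μ is 0.10 to 0.15 and the true level is 2[1 − Φ(3.29/√(1 + aμ))]. This is 0.0017 to 0.0022 at a = 1 and 0.0039 to 0.0063 at a = 3.

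**The case against.** The strongest reply is that the plan already deals with overdispersion. It names negative-binomial regression in advance for exactly that case, and the statistic and cut-off that decide it are a detail usually left to the analysis plan, which the article mentions and which is not at hand. This stands: the missing trigger is not in itself a fault, and a reader who infers that the plan ignores overdispersion would be wrong.

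Four further points also stand.
- A likelihood-ratio trigger keeps the error near 5%, and the stricter Pearson cut-offs largely do so once dispersion is 2 to 3 at 18 months. Inflation is therefore not a property of every common rule.
- The article gives no dispersion value, so every inflated figure is conditional on one.
- Differences between sites are absorbed by the site term, so only residual variation counts. The adjusted simulations show that the inflation persists for a given residual dispersion.
- The article is silent on the variance estimator. The Poisson figures assume model-based errors.

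A reader might also take "Other regression models will also be explored" as leaving the primary model open. That sentence stands under Sensitivity analyses and does not bear on the primary analysis.

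The objection does not remove the structure itself. Whatever trigger an analysis plan adds, this text lets the data choose the primary model, starting from the one that is not valid under foreseeable conditions.

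**Conclusion.** The point holds in a limited form. The plan fixes a Poisson default with a data-dependent switch, at an event rate where some common triggers would usually fail to fire. Under Pearson/df > 2 or deviance/df > 1, the type I error is about 7% to 14% for residual dispersion 1 to 3. It is about 6% to 7% at dispersion 0.5 if Poisson is kept, nominal at 0, and near nominal under a likelihood-ratio trigger.

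These figures rest on gamma-distributed rates between children, a null rate of 0.2 per year, the stated sample sizes, model-based Poisson errors and the assumed dispersion. They do not support the stronger inference that the trial will have an inflated error rate, because neither the dispersion nor the trigger is known. They do support removing the switch, because a single model that holds its level at every dispersion tried is available at almost no cost.

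**What to change.** In the sections on analysis populations, efficacy and secondary efficacy outcomes, name one model to be used whatever dispersion is observed. Either of these will do:
- negative-binomial regression with treatment, site and weight band, and log follow-up time as offset; or
- Poisson regression with the same terms and offset, and a robust (sandwich) variance per child.

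Apply it at the interim analysis and to the count secondary outcomes as well. Keep Poisson with model-based errors as a sensitivity analysis.

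The cost is a change of wording. Confidence intervals may be slightly wider when overdispersion is small. If overdispersion is larger, a valid analysis will also show the power that the Poisson sample size did not allow for. With 219 per arm over 18 months, SE = √[(1/0.3 + a)/219 + (1/0.15 + a)/219] and power = Φ(ln 2/SE − 1.96). This gives 90% at a = 0, 87% at 0.5, 84% at 1, 78% at 2 and 73% at 3. That loss comes from the variation between children and is not caused by the change of model.
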